## Abstract

**Background:**

Stroke is one of the most frequent diseases, and half of the stroke survivors are left with permanent impairment. Prediction of individual outcome is still difficult. Many but not all patients with stroke improve by approximately 1.7 times the initial impairment, that has been termed proportional recovery rule. The present study aims at identifying factors predicting motor outcome after stroke more accurately than before, and observe associations of rehabilitation treatment with outcome.

**Methods:**

The study is designed as a multi-centre prospective clinical observational trial. An extensive primary data set of clinical, neuroimaging, electrophysiological, and laboratory data will be collected within 96 h of stroke onset from patients with relevant upper extremity deficit, as indexed by a Fugl-Meyer-Upper Extremity (FM-UE) score ≤ 50. At least 200 patients will be recruited. Clinical scores will include the FM-UE score (range 0–66, unimpaired function is indicated by a score of 66), Action Research Arm Test, modified Rankin Scale, Barthel Index and Stroke-Specific Quality of Life Scale. Follow-up clinical scores and applied types and amount of rehabilitation treatment will be documented in the rehabilitation hospitals. Final follow-up clinical scoring will be performed 90 days after the stroke event. The primary endpoint is the change in FM-UE defined as 90 days FM-UE minus initial FM-UE, divided by initial FM-UE impairment. Changes in the other clinical scores serve as secondary endpoints. Machine learning methods will be employed to analyze the data and predict primary and secondary endpoints based on the primary data set and the different rehabilitation treatments.

**Discussion:**

If successful, outcome and relation to rehabilitation treatment in patients with acute motor stroke will be predictable more reliably than currently possible, leading to personalized neurorehabilitation. An important regulatory aspect of this trial is the first-time implementation of systematic patient data transfer between emergency and rehabilitation hospitals, which are divided institutions in Germany.

**Trial registration:**

This study was registered at ClinicalTrials.gov (NCT04688970) on 30 December 2020.

## Background

Stroke is one of the most common neurological diseases, which leaves one third of patients dead and one third with lasting disabilities despite the best standard of medical care [1]. Up to 70% of all acute stroke patients present with paresis of one upper extremity (UE) [2].

Recovery mostly occurs in the first weeks and plateaus at approximately three months after stroke. Up to 70% of recovery occurs spontaneously as a result of a sensitive phase of enhanced neuroplasticity directly after stroke, independent of rehabilitative interventions [3]. Rehabilitative interventions try to make use of this sensitive period by starting as early as possible while the patient is still on the stroke unit (SU). However, fixed rehabilitation procedures are usually applied, largely irrespective of stroke type (e. g., lacunar vs. territorial infarction, ischemic vs. hemorrhagic stroke), location (e. g., cortical vs. subcortical), or severity. It is therefore not surprising that some patients benefit from rehabilitation treatment more than others. Outcome varies depending on volume and localization of stroke lesion, clinical severity of stroke and integrity of the corticospinal tract (CST) [4–6]. For instance, a lesion in the posterior limb of the internal capsule is associated with poorer outcome than a lesion in the primary motor cortex [7]. Preserved interhemispheric functional and effective connectivity between the primary motor cortex (M1) and the supplementary area (SMA) are predictive for better motor outcome [8, 9]. Slow oscillations in resting-state electroencephalography (EEG) and low-complexity high-amplitude transcranial magnetic stimulation (TMS)-evoked EEG responses (TEPs) are associated with poor overall outcome [10–12].

Acute stroke severity is routinely assessed by the National Institute of Health Stroke Scale (NIHSS, range 0–42, 0 indicates absence of a neurological deficit) [13]. The initial NIHSS is related to stroke outcome. For instance, an NIHSS < 3 predicts an excellent outcome after three months, while a score > 15 is associated with poor outcome [6]. There is mounting evidence that inflammation during the acute phase after stroke influences severity and outcome. Elevation of C-reactive protein (CRP), for example, is associated with poor long-term outcome [14, 15]. Other blood biomarkers potentially relevant for stroke outcome are electrolytes, d-dimers, N-terminal proBrain natriuretic peptide (NT-proBNP) and troponin [14, 16, 17].

In addition, the integrity of the corticospinal tract (CST) is crucial for motor outcome. Integrity of CST can be evaluated by motor evoked potentials (MEPs) which is indeed one of the most robust biomarkers for motor outcome in stroke [4, 18].

Despite years of research and clinical practice, up to date it is neither possible to predict motor outcome after stroke reliably, nor which rehabilitation treatment to select for optimal outcome [3], although there were several attempts: For example, Stinear and colleagues [4] created an algorithm (Predict Recovery Potential 2 (PREP 2)), that included testing of shoulder abduction and finger extension (SAFE), patient age as well as presence or absence of MEPs, that determined UE outcome correctly for 75% of their cases, while 25% were still incorrectly classified. Other studies demonstrated that most patients recover by approximately 70% compared to their initial impairment, which has been termed the proportional recovery rule [19]. However, not all patients behave in accord with this rule, a phenomenon that has not been fully elucidated [20].

The present study aims not only to close this knowledge gap but also strives to observe to what extent type and amount of rehabilitation treatment relates to improvement of hand/arm motor function in stroke.

Towards this end, we will collect an extensive set of clinical, electrophysiological, imaging and laboratory data during the acute phase of stroke, and dense clinical follow-up data during rehabilitation and 90 days after stroke. Furthermore, type and amount of applied rehabilitation treatment will be recorded. The complex data will be analyzed by machine learning algorithms to identify predictive patterns for favorable stroke outcome. This may eventually help defining personalized rehabilitation, i.e., which patient benefits best from which therapy, and to what extent.

## Methods

### Objectives

The objective of the present study is to identify factors predicting motor outcome after stroke more accurately than hitherto possible, and rehabilitation treatments that are associated with improvement of arm−/hand function in individual motor stroke patients, using machine learning algorithms.

Primary objective: To determine which factors of the primary data set within 96 h of stroke onset and which type and amount of rehabilitation treatment predict the primary endpoint, i.e., the change in the FM-UE defined as 90 days FM-UE minus initial FM-UE, divided by initial FM-UE impairment.

Secondary objectives: Secondary endpoints are the quality of life, independence and range of activity of the UE measured by stroke-specific quality of life (SS-QOL) scale, modified Rankin Scale (mRS), Barthel-Index (BI) and Action Research Arm Test (ARAT) 90 days after the stroke event compared to the initial scores in the acute phase.

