### Outcomes

The primary endpoint is the percentage change in the FM-UE defined as 90 days FM-UE minus initial FM-UE, divided by initial FM-UE impairment:$$\frac{\mathrm{FMUE}\left(90\ \mathrm{days}\right)-\mathrm{FMUE}\left(\mathrm{initial}\right)}{66-\mathrm{FMUE}\left(\mathrm{initial}\right)}\times 100\%$$

The FM-UE [25] is a highly standardized, reliable and validated clinical score to assess deficits in upper extremity function after stroke [26]. The primary endpoint will allow to measure to what extent a given participant will deviate from the predicted proportional recovery rule of 70% improvement of the initial FM-UE impairment [19].

Secondary endpoints are the changes in the following tests 90 days after the stroke event compared to the initial test results within 96 h after stroke onset:Action research arm test (ARAT) [21]: to measure recovery of function of the UEModified Rankin scale (mRS) [22]: to measure neurological impairmentBarthel index (BI) [23]: to measure performance in activities of daily livingSS-QOL scale [24]: to measure quality of life and demonstrate the influence of the scores described above on the personal experience of the patient

All of these tests have shown reliability and have been validated in the assessment of patients post-stroke [22, 24, 27, 28].

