### Statistical methods

Statistical methods for primary and secondary outcomes.

Only those participants will a complete data set (including the 90 days follow-up examination or a lethal outcome) will be included in the statistical data analysis. Previous studies suggested that the FM-UE endpoints (i.e., the change in FM-UE 90 days after the stroke event compared to the initial FM-UE, see definition under “Outcome”) or the recovery trajectories of FM-UE scores can be clustered into 3 to 5 subgroups [4, 40]. We will first use time series clustering methods such as mixture of Gaussian processes [41] to identify such subgroups, then use the inferred cluster labels to build a classifier using lasso-regularized logistic regression to predict the group membership of the patient as a function of the primary data set and rehabilitation data set detailed in Tables 2, 3. The lasso regularization can automatically select a sparse subset of the significant features, reducing the dimensionality of the feature space and potentially the sample size required. We will use a nested-cross validation setup to tune the regularization strength via the 1SE-rule [29]. We can then use the Gaussian process model of the respective group to predict the primary endpoint and obtain estimates of the fraction of the explained variance of the total variance in the primary end point on data not seen during model training. If the linear model proves insufficient or unsatisfying, we will resort to non-linear regression models such as Generalized Additive Models (GAMs), which allow flexible nonlinear transformations of individual features of pairs of features [42]. Models for secondary endpoints will be built as well.

Interim analyses are not planned since this an observational study without interventions. No further analyses are planned apart from what is described under statistical methods for primary and secondary endpoints. Biobanking of blood samples will allow future (not yet planned) analyses of the relation of blood markers to stroke rehabilitation outcome.

Methods in analysis to handle protocol non-adherence and any statistical methods to handle missing data.

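### The aim is prediction more accurate than existing methods, but the planned explained variance cannot show a gain over the cited SAFE/age/MEP algorithm, because no such predictor is scored in the same patients

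*Protocol article*

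**What the plan says.** The comparative aim appears in three places in the protocol article. The Objectives section opens with the wish to "identify factors predicting motor outcome after stroke more accurately than hitherto possible". The Background paragraph of the Abstract says much the same, and the Discussion paragraph of the Abstract describes success as an outcome that "will be predictable more reliably than currently possible".

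The labelled primary objective, in the same Objectives section, is narrower. It begins "To determine which factors of the primary data set within 96 h of stroke onset and which type and amount of rehabilitation treatment predict the", and what is to be predicted is the FM-UE recovery ratio. It names no comparator.

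The Background section gives the state of the art. PREP 2, built on SAFE, age and MEP status, "determined UE outcome correctly for 75% of their cases, while 25% were still incorrectly classified". The second predictor is the observation that "most patients recover by approximately 70% compared to their initial impairment, which has been termed the proportional recovery rule".

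The Sample size and Statistical methods sections plan nested cross-validation and report held-out explained variance in the primary endpoint for the study's own models. Neither section applies an existing predictor to the study patients. Statistical methods then adds: "No further analyses are planned apart from what is described under statistical methods for primary and secondary endpoints".

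**The concern.** A claim of better prediction needs a reference predictor, judged on the same patients and the same scale. Under the plan, the reader would receive one explained-variance figure from this cohort and would have to set it against a classification accuracy from a different cohort. The two figures differ in metric and in case mix.

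What is at stake is the accuracy claim and, with it, a practical question: do EEG, imaging and laboratory data add anything to a short bedside set of SAFE, age and MEP status? A list of features kept by the lasso does not measure that gain in held-out accuracy.

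**Working it through.** The document offers no figure to reproduce here. The 75% comes from a cited source, and the Sample size section gives no formal calculation. Three checks apply.

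**1. The 70% rule on the ratio endpoint.** The endpoint (Outcomes section) is recovery as a percentage of initial impairment, so the rule predicts the constant 70 for everyone. For a constant predictor,

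R² = 1 − [SD² + (mean − 70)²]/SD² = −(mean − 70)²/SD².

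This is 0 if mean recovery is 70% and negative otherwise. With assumed values:
- mean 60, SD 45: −100/2025 = −0.05
- mean 50, SD 25: −400/625 = −0.64

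A held-out R² clearly above 0 therefore already means a smaller squared error than this rule on the ratio scale. The bar is low, and the result does not carry over automatically to FM-UE points. An error in points is the ratio error times initial impairment, which runs from 66 − 50 = 16 to 66 − 0 = 66. Squared errors are thus reweighted by up to 66²/16² = 4356/256 ≈ 17.

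**2. Translating 75% accuracy into R².** Simulation with 400,000 patients and a four-category rule that is right 75% of the time, each predicted category being given its mean recovery. Category means, shares, within-category SDs and error patterns are assumptions, not document figures.

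| Category means (%) | Shares | SD within | R², errors to adjacent category | R², errors at random |
|---|---|---|---|---|
| 10, 35, 65, 90 | 0.2, 0.2, 0.3, 0.3 | 10 | 0.73 | 0.40 |
| 10, 35, 65, 90 | 0.2, 0.2, 0.3, 0.3 | 20 | 0.56 | 0.30 |
| 10, 40, 70, 80 | 0.25, 0.15, 0.3, 0.3 | 20 | 0.56 | 0.30 |
| 5, 70, 75, 80 | 0.3, 0.1, 0.3, 0.3 | 15 | 0.63 | 0.39 |

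The same accuracy maps to R² between about 0.30 and 0.73. A study result of, say, 0.45 could be better or worse than PREP 2. Sampling error comes on top: at n = 200 the large-sample 95% half-width, 1.96 × √[4R²(1 − R²)²/n], is about 0.09 to 0.11 for R² between 0.3 and 0.6.

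**3. What a paired comparison would deliver.** Assume R² of 0.40 (reference) and 0.50 (study model), so residual variances are 0.6 and 0.5 of the total, with residual correlation ρ. With normal residuals, the total variance taken as known and model-fitting variability ignored,

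h = 1.96 × √{[2(0.6²) + 2(0.5²) − 4ρ²(0.6)(0.5)]/n} = 1.96 × √[(1.22 − 1.2ρ²)/n].

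The chance that the interval excludes zero when the true gain is 0.10 is about Φ(1.96 × 0.10/h − 1.96), using the simulated h.

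| n | ρ | h, formula | h, simulated | Chance of excluding zero |
|---|---|---|---|---|
| 200 | 0.70 | 0.110 | 0.110 | 43% |
| 200 | 0.85 | 0.082 | 0.083 | 66% |
| 120 | 0.70 | 0.142 | 0.141 | 28% |
| 120 | 0.85 | 0.106 | 0.106 | 46% |

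The target is 200. The 120 is an assumption, shown because Statistical methods restricts the analysis to participants with complete data.

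**The case against.** Much of the case on the other side stands.

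- **The labelled primary objective is not comparative.** It asks which factors predict, the Trial design section calls the framework exploratory, and the Abstract's success statement is conditional. A reader might infer that the study cannot answer its question. The documents do not support that: lasso selection with held-out explained variance suits the primary objective, and only the accuracy claim is affected.
- **One benchmark is already covered.** The Outcomes section says the endpoint shows how far a participant will "deviate from the predicted proportional recovery rule of 70% improvement of the initial FM-UE impairment", and check 1 shows that a positive R² beats that constant. It would be wrong to say that no existing rule can be compared.
- **A classifier is planned.** Statistical methods clusters patients into subgroups and predicts membership by lasso logistic regression, so held-out group accuracy could be computed. This helps only in part. The article does not list accuracy as a reported figure, and subgroups inferred from this cohort need not match the categories behind the 75%.
- **The closing sentence on further analyses may be narrower than it looks.** It follows the statement on interim analyses, and a benchmark could be seen as part of evaluating the primary-endpoint model. The article also condenses a full protocol that is not shown. A reader might infer that benchmarking is forbidden, but the text does not go that far. It does present the described methods as the whole plan, and they include no reference predictor.
- **Precision is modest.** In three of the four scenarios in check 3 the half-width exceeds the assumed gain of 0.10. A paired comparison is therefore no guarantee of a clear answer.

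**Conclusion.** The point holds for the comparative accuracy claim measured against the SAFE/age/MEP algorithm. It does not hold for the primary objective, nor for the 70% rule on the ratio scale. The planned explained variance cannot show improvement over PREP 2, because 75% accuracy in other patients has no fixed equivalent on that scale (about 0.30 to 0.73 under the assumed structures). A same-fold comparison would supply the missing evidence, although a gain of 0.10 would be borderline at 200 patients and more likely missed than found at an assumed 120. These sizes rest on the assumed R² values, residual correlations and category structures. The finding that no reference predictor is scored rests on the text alone.

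**What to change.** In Statistical methods, add that the following are scored in the identical outer folds:

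1. the 70% rule, with error also expressed in FM-UE points;
2. a model using only SAFE, age and MEP status, labelled as a proxy for PREP 2. It is not PREP 2 itself, because it is refitted to this cohort and the article does not give PREP 2's decision rules.

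Compare both with a version of the study model restricted to the primary data set from the first 96 hours. Report the model with rehabilitation data separately: it uses post-acute information, including repeated FM-UE scores, which an acute-phase rule does not have. Mixing the two would hide what the acute markers add.

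Report paired differences in held-out error and R², and held-out group accuracy for the planned logistic classifier, all with 95% intervals. Claim greater accuracy only if the interval for the difference excludes zero. Otherwise limit the conclusion to which factors predict.

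The cost is a little more analysis and no new data: SAFE and MEP are in Table 2, and age is needed for eligibility. The downside is that the accuracy claim may turn out not to be supported.

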### Trial design

MWKNeuroReha is designed as a multi-centre prospective observational clinical trial. The framework is exploratory. The study was registered at ClinicalTrials.gov (NCT04688970, registry name: Personalized Neurorehabilitative Precision Medicine – From Data to Therapies) on 30 December 2020 and is expected to completed 31 December 2022.

For more administrative information see Table 1.

**Table 1 Tab1:** Administrative information

Title	Personalized neurorehabilitative precision medicine: from data to therapies (MWKNeuroReha) – a multi-centre prospective observational clinical trial to predict long-term outcome of acute stroke patients with acute motor stroke	
Trial registration	ClinicalTrials.gov Identifier: NCT04688970 Registry name: Personalized Neurorehabilitative Precision Medicine – From Data to Therapies Date of registration: 30 December 2020 Secondary identifying numbers: BNP-2020-09 Contact for public and scientific queries: [name] and [name], University Hospital of Tübingen, Department for Neurology & Stroke and Hertie Institute for Clinical Brain Research; phone: [name]; e-mail: [contact] Countries of recruitment: Germany Health condition studied: acute stroke with affection of the UE Interventions and study type: observational study (no interventions) Key inclusion and exclusion criteria: • Ages eligible for study: ≥18 years • Sexes eligible for study: both • Accepts healthy volunteers: no • Main inclusion criterion: acute motor stroke with functional relevant deficit of the UE • Main exclusion criteria: no acute stroke, no relevant affection of UE, contraindication to MEPs Date of first enrolment: 01 December 2020 Target sample size: 200 patients Recruitment status: recruiting Primary outcome: percentage change in the FM-UE defined as 90 days FM-UE minus initial FM-UE, divided by initial FM-UE impairment: $$\frac{\mathrm{FMUE}\left(90\ \mathrm{days}\right)-\mathrm{FMUE}\left(\mathrm{initial}\right)}{66-\mathrm{FMUE}\left(\mathrm{initial}\right)}\times$$ Secondary outcome: • Action research arm test (ARAT) [21]: to measure recovery of function of the UE • Modified Rankin scale (mRS) [22]: to measure neurological impairment • Barthel index (BI) [23]: to measure performance in activities of daily living • SS-QOL scale [24]: to measure quality of life and	
Protocol version	Issue dates: 21 Sep 2020 (original protocol) / 23 Nov 2020 (protocol amendment 1) Protocol amendment Number: 01 Authors: CB, UZ	

### Participants, interventions and outcomes

#### Study setting

The study will take place in the University Hospital of Tübingen (southwest Germany). In this tertiary referral hospital > 1000 acute stroke patients are treated every year. The University Hospital of Tübingen is the lead partner of the Centre for Neurovascular Diseases, a network of seven cooperating acute-care hospitals to provide optimal treatment for stroke and other neurovascular diseases. Four of these hospitals will act as additional study sites for recruitment of acute stroke patients. The acute-care hospitals collaborate with seven neurorehabilitation hospitals where the acute stroke patients of this study are transferred to for rehabilitation treatment.

#### Eligibility criteria

Inclusion criteria:18 years or aboveAcute motor stroke with functionally relevant UE deficit (FM-UE ≤ 50)Participant understands the study and its procedures and provides written informed consentIf the participant is not able to provide informed consent:∘The assumed will of the patient is assessed by the participant’s provision (if existing), the health care proxy (if existing) and/or the will that has been expressed by the patient to close relatives∘The legal representative provides written informed consent based on this assessment

Exclusion criteria:Less than 18 years oldNo acute stroke, or stroke does not affect UE function, or FM-UE > 50Participant or legal representative do not provide written informed consentParticipant has an intracranial implant (e.g., aneurysm clips, shunts, stimulators, cochlear implants, or electrodes) or any other metal object within or near the head (excluding the mouth) that cannot be safely removedParticipant has a history of any illness that, in the opinion of the study investigator, might confound the results of the studyAny concern by the investigator regarding the safe participation of the participant in the study, or any other reason because of which the investigator considers the participant inappropriate for study inclusionPregnancyParticipant refuses to receive neurorehabilitation treatment

Besides, a blood sample (10 ml) will be obtained and stored in the local biobank of the Medical Faculty of the University of Tübingen/University Hospital of Tübingen for possible further retrospective analyses. Extra written informed consent will be obtained from each participant.

Medical doctors will screen the patients for participation, explain the study to them, answer their questions and finally obtain their written informed consent, provided the patients or their representatives understand the purpose and procedures of the study, are able to provide written informed consent and are willing to participate.

